## 3. Methods

### 3.1. Design

A four-site randomised controlled trial will be conducted to investigate the short- and long-term physiological and neurobehavioral effects of EVC.

### 3.2. Study Setting

Infants will be recruited from four university hospitals in Italy: Careggi University Hospital (Florence), NICU Fondazione IRCCS Ca’ Granda Ospedale Maggiore Policlinico (Milan), Modena University Hospital (Modena), and Bologna University Sant’Orsola-Malpighi Hospital (Bologna), and randomised to either an intervention or control group. Infants in the intervention group will receive EVC from the mother, whereas in the control group, mothers will be encouraged to spend the same amount of time next to the incubator, observing their infant’s behaviour through a standard cluster of indicators. The randomisation sequence, unique for the four centres, is led by the Statistical Office of the University of Modena and Reggio Emilia.

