## 1. Background

Preterm birth rates are continuously increasing in most countries and over 500,000 infants are born prematurely every year [1]. Despite rapid advances in technology, the number of preterm infants with low gestational age (GA) at birth, who demonstrate short- and long-term sequelae of prematurity before reaching school age remains high [2]. Approximately 40% of low birth weight preterm infants experience a complex spectrum of unfavorable neurodevelopment outcomes [3] compared with their full-term peers. Thus, prematurity is of great concern for health policies, in both low and high-income countries [4,5]. The aforementioned impaired development of preterm infants is associated with medical factors and partly a consequence of their atypical early-life environment, including uncontrolled sensory inputs, pain stressors, and early maternal separation [6,7,8] during their hospitalisation in the neonatal intensive care unit (NICU). 

Developmental care practices aim to minimise the stress of the NICU environment through specific interventions, which may include control of external sensory stimuli [9] pain and stress management, and increased family involvement in the preterm infant’s care [10]. Health policies for guidelines in the NICU are still inhomogeneous, especially regarding parental presence in the NICU and family-centred care. Specific guidelines have recently been published with the support of an interdisciplinary group of experts, comprising paediatricians, parents, neonatologists, psychologists, and therapists [11]. These, hopefully, will be broadly adopted in NICUs in the forthcoming years.

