### 3.3. Participants

Eighty preterm infants, born at 25–32 weeks and 6 days GA, will be recruited from the four centres (20 per centre). Recruitment will be undertaken in each centre by a trained research assistant (RA), who will review birth records daily. After obtaining permission from the attending physicians of both the mother and infant, the RA will invite qualifying families to participate and will obtain written informed consent from those enrolling. Infants will be then assigned to the EVC intervention or control group using a randomised design, stratifying infants by gender and GA (see Randomisation). Mothers whose infants are assigned to the control group will be asked to spend the same amount of time as that of mothers in the intervention group, observing their infants’ spontaneous behaviour, with the subsequent compilation of an observation grid developed ad hoc, according to few indicators drawn from The Neonatal Behavioural Assessment Scale. The mothers whose infants are assigned to the control group will be asked not to vocally interact with them during the observational intervention.

Recording sessions will take place midway between the feeding cycles, more than 1 h after the feed and more than 4 h after the last medical exam.

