### 3.8. Randomisation

A centralised patient randomisation will be performed using a secure, web-based randomisation system, through which the study investigator of each centre can register new patients and obtain the treatment arm assignment.

A block allocation sequence with variable block sizes (block size 2–4), stratified by GA and gender, will be generated using Stata statistical software (StataCorp, College Station, TX, USA) with the “ralloc” command. In case of twins, randomisation will be conducted at the level of the family (i.e., twins will be randomised to the same group). The allocation sequence will be concealed from the investigators.

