## 5. Outcome Measures

### 5.1. Primary Outcome Measure

#### Physiological Level

During the interventions, time and frequency analysis of HRV will be applied to the following parameters: LFpower (power in the LF band), HFpower (power in the HF band), LFnu (normalised power in the LF band [LF power/(LFpower + HFpower)]); HFnu (normalised power in the HF band [HF power/(LFpower + HFpower)]); LF% (percentage power in the LF band [LF power/total power]), HF% (percentage power in the HF band [HF power/total power]), and LF/HF (ratio between LF power and HF power). The change from baseline will be calculated across the three conditions (i.e., singing, speaking, and control).

HRV will be measured through the acquisition of the ECG signal, via electrodes placed on the infant’s chest by routine medical devices. Subsequently, the ECG signal will automatically be recorded by the IxTrend Software (Ixellence GmbH, Wildau, Germany). Moreover, the heart rate (beats per minute), oxygen saturation (%), and all critical events (hypoxemia, oxygen saturation <80%; bradycardia, heart rate <80 bpm) will be acquired during the different conditions using the relevant medical apparatus. 

The physiological level is strictly dependent on the infant’s behavioural state (i.e., quiet, active, indeterminate, awake, or crying), which will be assessed offline from the video-recorded sessions by blinded coders, according to the Prechtl scale [8]. Measures of physiological parameters will be collected over the intervention period, as well as 20 min before and after the mother’s intervention.

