### 8.2. Secondary Outcomes

To assess the effect of EVC on the neurobehavioral and developmental outcomes of newborns, as well as on maternal stress and presence in the NICU, the values for the different scales and questionnaires will be compared (at the time points specified in the Secondary Outcome Measures) between the intervention and control groups. Confounding variables will be entered in the analysis (i.e., familiar socio-economical score, gestational age at birth) to partial out any effect which they could have on the difference between the outcome measures. For continuous variables the Wilcoxon-Mann-Whitney test will be applied, while for categorical variables the chi-squared test (or Fisher’s exact test where appropriate) will be applied. 

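### Centre enters neither the allocation strata nor any stated between-arm comparison in this four-centre trial; the tests stay valid, but accounting for centre in the analysis would recover precision at almost no cost

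*Protocol article*

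**What the plan says.** **Allocation.** Section 3.2 (Study Setting) states: "The randomisation sequence, unique for the four centres, is led by the Statistical Office". Section 3.8 (Randomisation) adds "A centralised patient randomisation will be performed using a secure, web-based randomisation system" and "A block allocation sequence with variable block sizes (block size 2–4), stratified by GA and gender". Section 3.3 (Participants) gives the same two factors, "using a randomised design, stratifying infants by gender and GA (see Randomisation", and plans 20 infants in each of the four centres, 80 in all.

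**Analysis.** For the primary outcome, section 8.1 compares the two arms with a Kruskal–Wallis test on HRV parameters from the first five minutes of each session. It names no centre term. For the secondary outcomes, section 8.2 says "Confounding variables will be entered in the analysis (i.e., familiar socio-economical score, gestational age at birth"; the list is introduced by i.e. and does not include centre. The tests named there are Wilcoxon–Mann–Whitney, chi-squared and Fisher's exact.

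**What bears on centre.** The Background (section 1) remarks that "Health policies for guidelines in the NICU are still inhomogeneous, especially regarding parental presence in the NICU and family-centred care". Section 5.1 records the ECG by electrodes on the "chest by routine medical devices", and names one common recording software. Section 4.1.3 measures background noise in each centre at every session to check audibility, and rules out further analysis of the values.

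**The concern.** Centre is a natural source of variation in a multicentre neonatal unit trial, and here it is handled at neither stage. Nothing in the allocation balances the arms within a centre, and nothing in the stated analyses removes differences between centres afterwards.

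Two secondary outcomes are especially exposed. Maternal presence in the unit (section 5.2.2) depends on visiting policy, which is the feature the Background singles out as varying between units. PSS-NICU (section 4.1.2) has one domain on the sights and sounds of the unit, so it partly scores the unit itself. The HRV outcome could carry differences between devices.

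Two things are at stake. A chance imbalance in one centre moves part of that centre's deviation into the estimated EVC effect. Even with balanced arms, between-centre variation stays in the error term and lowers power.

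**Working it through.** **1. The plan's own sample size.** Inputs from section 3.7: HF 15 (SD 2.6) against 17 (SD 2.4), low-frequency (LF) 31 against 25 (SD 4.9), alpha 0.025. The stated beta of 0.80 is read as power, and alpha as two-sided.

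n per group = 2 × SD² × (z for alpha/2 + z for power)² / difference², with z values 2.241 and 0.842.
- HF, pooled SD √((2.6² + 2.4²)/2) = 2.50: 2 × 6.25 × 9.505 / 4 = 29.7, so 30.
- HF by the noncentral t with SD 2.4: 29, which matches the plan.
- LF: 2 × 24.01 × 9.505 / 36 = 12.7, so 13.

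HF therefore drives the size. With a 20% loss, 80 × 0.8 = 64 infants remain, or 32 per arm.

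**2. Balance within centres.** The stated scheme was simulated: four centres of 20, one sequence per GA-by-gender stratum shared by all centres, and permuted blocks of 2 or 4. The number of GA bands is not given, so 2, 3 and 4 were tried, with 4,000 runs each.

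| GA bands (strata) | Given centre 13:7 or worse | Any centre 13:7 or worse | Any centre 14:6 or worse |
|---|---|---|---|
| 2 (4) | 20% | 53% | 22% |
| 3 (6) | 20% | 53% | 23% |
| 4 (8) | 20% | 55% | 24% |

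A separate run of 20,000 allocations with four strata gave 53% and 23%. The result hardly depends on the number of bands. Twins, who are randomised together, were not simulated and could add to the imbalance.

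**3. What an imbalance does.** With 40 per arm, a centre split 13:7 passes (13 − 7)/40 = 0.15 of its deviation into the arm difference. Over all four centres, the 95th percentile of the chance shift was 0.09, 0.13 and 0.18 SD at an assumed centre ICC of 0.05, 0.10 and 0.20. The design difference for HF is 2/2.5 = 0.80 SD.

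**4. Validity.** Under no treatment effect, the unadjusted rank test at the 0.025 level rejected in 2.7%, 2.2% and 2.4% of runs at those three ICCs. Type I error is kept.

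**5. Precision.** Take the stated SD as the total SD, so that accounting for centre leaves SD × √(1 − ICC). Power at 32 per arm is Φ(2 / (SD × √(2/32)) − 2.241).

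| Assumed ICC | SD left | Power, HF |
|---|---|---|
| centre ignored | 2.50 | Φ(3.200 − 2.241) = 83% |
| 0.05 | 2.44 | Φ(3.283 − 2.241) = 85% |
| 0.10 | 2.37 | Φ(3.373 − 2.241) = 87% |
| 0.20 | 2.24 | Φ(3.578 − 2.241) = 91% |

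This formula is for a comparison of means and only approximates the planned rank tests. The documents give no ICC.

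**The case against.** **The centres are not shown to differ.** The remark in the Background is about neonatal units in general. The ECG signal goes to one software package, and noise is measured with one meter model. A reader might infer that these four hospitals are known to differ in equipment, noise and policy. The article does not say so; it supports only that they may. This objection stands.

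**Leaving centre out of the strata is defensible.** Centre by gender by two GA bands would give 16 strata of 80/16 = 5 infants. With blocks of 2–4 and no blinding at the bedside, assignments within a centre would be easier to predict. Stratifying by centre would cut the chance of a 13:7 split in any centre to 0.5% (4% or 13% with three or four GA bands), but at that price. A reader might infer that the allocation scheme is an error; it is a reasonable trade-off. This also stands, and it makes the analysis the place to deal with centre.

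**Change from baseline may absorb centre differences.** Section 5.1 plans a change from baseline, and several HRV parameters are ratios, so stable device differences would partly cancel. This holds in part: section 8.1 compares session values between arms, and maternal presence has no baseline to subtract.

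**An unseen analysis plan might add centre.** It might. But the article names the primary test and gives what reads as a closed list of confounders, so the point concerns what is stated and not a detail left out.

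**The word unique might mean one sequence per centre.** Neither statement of the strata includes centre ("stratified by GA and gender, will be generated using Stata statistical software"), so a single shared sequence is the better reading.

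**Conclusion.** The point holds as a matter of precision. As stated, the plan gives a better-than-even chance (about 53%, with four strata assumed) that at least one centre ends 13:7 or worse, and about 23% for 14:6 or worse. No stated analysis then takes account of centre.

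A stronger reading, that the comparison is biased or the test invalid, is not supported. Allocation is random, type I error stays near 0.025, and the chance shift is modest beside the HF effect the trial is designed to detect. Power with centre ignored is about 83% at 32 per arm, already above the 80% target. The gain is therefore useful but not decisive for HF: 2, 4 or 8 percentage points at an ICC of 0.05, 0.10 or 0.20.

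The gain is likely to be greatest for maternal presence and PSS-NICU, where the outcome partly reflects the unit. That is a judgement from the nature of these outcomes, because the documents give no variance figures for them. All precision figures rest on assumed ICCs.

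**What to change.** Before outcome data are examined by arm, state in sections 8.1 and 8.2 that every between-arm comparison accounts for centre (four levels):
- **Continuous outcomes, including HRV, maternal presence and PSS-NICU:** a van Elteren test (Wilcoxon stratified by centre), or a model with centre as a fixed effect. In the secondary analyses, the model can carry centre beside the socio-economic score and GA already named.
- **Categorical outcomes:** a centre-stratified test such as Cochran–Mantel–Haenszel.

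Leave the allocation scheme as it is. The cost is a few lines of text and three degrees of freedom out of about 80 infants, with no extra patients or procedures. The change can be made even if recruitment is complete. If centre explains almost nothing, the loss is those three degrees of freedom.

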### 3.3. Participants

Eighty preterm infants, born at 25–32 weeks and 6 days GA, will be recruited from the four centres (20 per centre). Recruitment will be undertaken in each centre by a trained research assistant (RA), who will review birth records daily. After obtaining permission from the attending physicians of both the mother and infant, the RA will invite qualifying families to participate and will obtain written informed consent from those enrolling. Infants will be then assigned to the EVC intervention or control group using a randomised design, stratifying infants by gender and GA (see Randomisation). Mothers whose infants are assigned to the control group will be asked to spend the same amount of time as that of mothers in the intervention group, observing their infants’ spontaneous behaviour, with the subsequent compilation of an observation grid developed ad hoc, according to few indicators drawn from The Neonatal Behavioural Assessment Scale. The mothers whose infants are assigned to the control group will be asked not to vocally interact with them during the observational intervention.

Recording sessions will take place midway between the feeding cycles, more than 1 h after the feed and more than 4 h after the last medical exam.

### 3.4. Patient and Public Involvement Statement

Patients were not involved in the design and conduct of the study, nor in the choice of outcome measures. They will be involved at the first stage of the recruitment (see *Participants*).

### 3.5. Inclusion Criteria

The inclusion criteria for the newborns will be: GA between 25 + 0 and 32 + 6 weeks at birth; Apgar score ≥ 7 at 10 min; birth weight between 3rd and 97th percentiles; birth cranial circumference greater than 10th percentile; periventricular leukomalacia (PVL) grade 1; intraventricular haemorrhage (IVH) grade 1–2; and hypoglycaemia, hyponatraemia, and hypocalcaemia are permitted, provided they are not persistent and severe. 

### 3.6. Exclusion Criteria

The exclusion criteria for the newborns will be: PVL grade III and IV, IVH grade III and IV, sepsis (vertical and horizontal), congenital malformations and/or genetic abnormalities, requiring respiratory support with high flow/nCPAP repeated apnoea associated with bradycardia and fall of saturation, hyaline membrane disease, respiratory distress syndrome, and hyperbilirubinaemia requiring exchange transfusions during hospitalisation. 

Lack of informed consent will exclude the infant from the study.

The exclusion criteria for the mothers will be presence of depressive symptoms, drug abuse, and age below 18 years.

### 3.7. Sample Size and Power Analysis

The main outcome measures for the primary outcome will be the low-frequency (LF) and high-frequency (HF) power of the HRV measure. We expect the baseline measurement mean value (±standard deviation) of LF and HF power for preterm infants to be 31 ± 4.9 Hz and 15 ± 2.6 Hz, respectively [58]. We assume that the treatment in the experimental population is effective if the mean values of LF and HF power reach 25 ± 4.9 and 17 ± 2.4 Hz, respectively. 

With an alpha setting at 0.025 and beta setting at 0.80, it is necessary to enroll 29 patients per group. Assuming a 20% loss, we aim to enroll at least 80 patients total (40 per group).

### 3.8. Randomisation

A centralised patient randomisation will be performed using a secure, web-based randomisation system, through which the study investigator of each centre can register new patients and obtain the treatment arm assignment.

A block allocation sequence with variable block sizes (block size 2–4), stratified by GA and gender, will be generated using Stata statistical software (StataCorp, College Station, TX, USA) with the “ralloc” command. In case of twins, randomisation will be conducted at the level of the family (i.e., twins will be randomised to the same group). The allocation sequence will be concealed from the investigators.

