## 8. Statistical Analyses

### 8.1. Primary Outcome

The modulation of vagal activity will be tracked as a function of time during the interaction between the infants and mothers, by calculating the LF and HF power of the HRV and investigating respiratory sinus arrhythmia. The acquired autonomic signals (e.g., ECG, PPG, and breath signal) will be analysed to evaluate the differences between the physiological responses related to the different experimental groups. Standard analysis techniques that involve the extraction of parameters in the time and frequency domain will be applied in the first instance. 

Intra-group analysis (considering the control group and the intervention group separately) will be performed with the Friedman test by comparing the values of HRV parameters extracted from the three sessions (pre, yes and post). Post-hoc correction (Bonferroni method) will be applied. Inter-group analysis (between the control group and the intervention group) will be performed with the Kruskal–Wallis test by comparing HRV parameters of the first five-minute window of each session (pre, yes and post) between the two groups. Finally, innovative methods of analysis aimed at applying the chaos theory to physiological signals will be used to study the complexity of autonomic dynamics and the nonlinear coupling between the autonomic subsystems. These nonlinear analysis techniques will be applied both univariate (using a single signal, preferably HRV) and multivariate (e.g., considering HRV and pulse rate variability at the same time) domains.

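### Twins are randomised as a family, but the between-group tests and the sample size for infant outcomes treat infants as independent

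*Protocol article*

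**What the plan says.** All references are to the protocol article.

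- **Allocation (Section 3.8).** "In case of twins, randomisation will be conducted at the level of the family (i.e., twins will be randomised to the same group". For twins, the randomised unit is therefore the family.
- **Primary comparison (Section 8.1).** "Inter-group analysis (between the control group and the intervention group) will be performed with the Kruskal–Wallis test", applied to HRV parameters. No family term is mentioned.
- **Secondary comparisons (Section 8.2).** "For continuous variables the Wilcoxon-Mann-Whitney test will be applied", with chi-squared or Fisher's exact test for categorical outcomes. The adjustment variables named are socio-economic score and gestational age (GA) at birth. Family and twin status are not among them.
- **Sample size (Section 3.7).** "With an alpha setting at 0.025 and beta setting at 0.80, it is necessary to enroll 29 patients per group". The article then adds: "Assuming a 20% loss, we aim to enroll at least 80 patients total (40 per group". The inputs are infant-level means and standard deviations. No twin share, within-family correlation or design effect appears.

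**The concern.** Co-twins always land in the same arm, so positive correlation between them adds directly to the variance of the between-arm difference and cannot cancel out. The article itself gives reasons to expect such correlation. Co-twins have the same GA at birth, and Section 2 says GA correlates with HRV. They also have the same mother, who delivers the intervention, and the same family socio-economic score.

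The named rank and chi-squared tests compute their null variance as if every infant were independent. Where pairs are enrolled and correlate positively, that variance is too small, and so are the p-values for infant outcomes. The required number was likewise derived as if 29 infants carried 29 independent pieces of information.

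This is more than detail left to a statistical analysis plan. The article fixes both a clustered allocation and tests that cannot accommodate it. An analysis plan that follows the named tests inherits the problem, and one that does not departs from the protocol.

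**Working it through.** **1. Reproduce the plan's figure.** The inputs come from Section 3.7: baseline LF and HF of "31 ± 4.9 Hz and 15 ± 2.6 Hz, respectively", and a treatment effect if "the mean values of LF and HF power reach 25 ± 4.9 and 17 ± 2.4 Hz, respectively". I read the 0.80 labelled beta as power, and alpha 0.025 as two-sided, which fits the stated number.

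- HF: difference 2; pooled SD = √((2.6² + 2.4²)/2) = 2.50; standardised difference 2/2.50 = 0.80.
- n per group = 2 × (2.241 + 0.842)² × (2.50/2)² = 29.75, so 30, within rounding of the stated 29.
- LF: difference 6, SD 4.9. The same formula gives 12.7, so 13 per group. HF therefore drives the sample size.
- Loss: 29/0.8 = 36.25, so 37 per group, which the plan rounds up to 40. After 20% loss, 40 × 0.8 = 32 per group remain.

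The stated figure reproduces with no clustering term.

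**2. Design effect.** Let f be the share of infants enrolled together with their co-twin, and ICC the within-pair correlation. The variance of an arm mean is multiplied by

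DE = 1 + f × ICC.

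The article gives neither input, so both are assumptions here: f from 0.1 to 0.4 and ICC from 0.3 to 0.7. A twin enrolled without the co-twin does not count towards f.

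**3. True size of a test that ignores families.** For a two-sided nominal level with critical value z, size = 2 × (1 − Φ(z/√DE)), with z = 2.241 for 0.025 and 1.960 for 0.05. Section 3.7 states 0.025; the 0.05 column is for illustration.

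**4. Power of a test at the correct size.** I used a noncentral t with effective n = n/DE per arm and two-sided alpha 0.025.

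| f | ICC | DE | Size, nominal 0.025 | Size, nominal 0.05 | HF power, 32/arm | HF power, 40/arm | LF power, 32/arm |
|---|---|---|---|---|---|---|---|
| no pairs | – | 1.00 | 0.025 | 0.050 | 81.4% | 89.9% | 99.5% |
| 0.1 | 0.3 | 1.03 | 0.027 | 0.053 | 80.0% | 88.9% | 99.3% |
| 0.2 | 0.3 | 1.06 | 0.029 | 0.057 | 78.7% | 87.9% | 99.2% |
| 0.2 | 0.5 | 1.10 | 0.033 | 0.062 | 77.0% | 86.6% | 99.0% |
| 0.3 | 0.5 | 1.15 | 0.037 | 0.068 | 74.9% | 84.8% | 98.7% |
| 0.4 | 0.7 | 1.28 | 0.048 | 0.083 | 69.5% | 80.3% | 97.6% |

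At 32 per arm, HF power stays at 80% up to a DE of about 1.03 by noncentral t, or about 1.076 by the normal approximation. At 40 per arm the limits are about 1.29 and 1.34.

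**5. Check on the planned test.** Kruskal–Wallis was simulated under the null with 32 per arm, nominal level 0.025 and 20,000 runs. The rejection rate was 0.023 with no twins, 0.031 (f 0.2, ICC 0.5), 0.036 (f 0.3, ICC 0.5) and 0.041 (f 0.3, ICC 0.7). The formula gives 0.025, 0.033, 0.037 and 0.042, so the two agree closely.

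**The case against.** The strongest reply is that the size rests on two quantities the article does not give, and that both could be small.

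- Both co-twins must separately pass the restrictive criteria of Sections 3.5 and 3.6, so the share enrolled in pairs may be well below the share who are twins.
- HRV depends on the individual infant's behavioural state (Section 5.1), and sessions take place at individual incubators or cribs (Section 3.9). The article does not say that co-twins share a session. The ICC for HRV could therefore be low.
- For secondary outcomes, GA and socio-economic score are already to be entered, and these are two of the factors that co-twins share.

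This stands as a limit on size. With 10% in pairs and an ICC of 0.3, 0.025 becomes only 0.027. It does not remove the mismatch between the allocation and the tests.

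Some stronger readings are tempting but not supported:

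- **That the 80% power is not delivered.** The primary outcome is recorded during two weeks in hospital, while follow-up runs to 24 months. The article does not say how the 20% loss divides, so between 32 and 40 per arm may be evaluable for HRV. At 40 per arm HF power is still 80.3% in the worst scenario above, and LF power is high throughout.
- **That every test is affected, with twin mothers counted twice.** Section 4.1.2 gives each mother one stress score per time point, and Section 5.2.2 collects NICU presence from the mother. Nothing says that her record is duplicated.
- **That stratifying by gender breaks down for opposite-sex pairs.** Section 3.8 does not say which stratum such a pair uses. That is an operational detail an article may leave to the full protocol, and no bias follows from what is written.

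**Conclusion.** The point holds for between-group tests of infant outcomes. As written, the plan gives p-values that are too small whenever both co-twins enrol and their outcomes correlate positively. Over the assumed range the inflation is modest: a nominal 0.025 becomes roughly 0.03–0.04 in the middle scenarios and 0.048 at the top. For HF at 32 per arm, power may fall from 81% to between 80% and 70%. With 40 evaluable per arm it holds at 80% or just above. LF power is not in question. The direction follows from the allocation rule together with the named tests. The size depends on an assumed share in pairs and an assumed ICC.

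**What to change.** - **Analysis (Sections 8.1 and 8.2).** For infant outcomes, replace the independent-infant between-group tests with a method that accounts for family. A clustered rank test keeps the planned rank-based approach. A family random intercept, or GEE or cluster-robust standard errors with a small-sample correction, would also serve but changes the class of model. Add one infant per family as a sensitivity analysis.
- **Sample size (Section 3.7).** Keep 80 infants. Restate HF power over an explicit range for the share enrolled in pairs and the within-pair ICC, and for 32 to 40 evaluable infants per arm.

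The cost is analysis and wording only, with no extra infants or visits. Intervals become slightly wider and the stated HF power slightly lower. The change should be settled before the comparative analysis.
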